### 3.7 What is the proposed duration of treatment (see interventions)

### 3.9 and 3.10. What are the proposed outcome measures, frequency and duration of follow-up?

- **Primary: Episodes of ILI and RTI, their duration and transmission in families.:** *We hypothesize that the intervention will reduce the number of episodes (by reducing transmission) and hence the number of days with symptoms.* During the feasibility phase we will pilot the use of both paper and web versions of illness diaries, and of monthly questionnaires (both web and paper based) with emailed reminders. Our preference is that index patients will be prompted by email to log onto the website monthly to complete questionnaires about illnesses during the last month since the duration of symptoms can be remembered reliably over a period of a few weeks. However those that prefer will be provided with a double sided A4 sheet (and spare sheets in case of families with frequent infections) to provide simple summary diary entries of respiratory tract infection, and will still get the monthly email prompt reminders. For each episode the index person will document: the nature of the infection; the duration of symptoms rated moderately bad (which we have shown is the most likely to be sensitive to change for individuals with cough and fever and can be remembered reliably over a period of a few weeks); the number of days where work/normal activities were impaired; whether other family members either had a similar infection before or after the index case, and what the time interval was; whether contact with the health service was needed; and (for the intervention group only) how well the index patient and other family members complied with the target behaviours. We have used diary sheets in our respiratory studies and found good levels of compliance. The monthly illness information will be supplemented by a questionnaire at the end of the winter (April) documenting the summary information, and which can be validated against the monthly information. We are currently using a similar end of winter questionnaire in a study of respiratory and ear infections in families (the 'PIPO' study <http://www.controlled-trials.com/ISRCTN53286030>), and shown it to be feasible and reliable; this questionnaire will particularly provide some information for those individuals not returning their diary or monthly questionnaires. Our experience with questionnaires is supported by illness transmission studies where similar questionnaires/diaries have been used. An illness will be classified based on the records as a potential ILI based on reported fever (or measured temperature >37.5), plus a respiratory symptom (sore throat, cough, coryza) plus a systemic symptom (prostration, headache, severe fatigue, severe muscle aches, severe malaise) i.e. using an analogous definition to the diagnostic sub-study. We will base our definition of RTI on consensus definitions developed in previous studies - which have defined a respiratory tract infection as 2 symptoms of an RTI for at least 1 day or 1 symptom for 2 consecutive days. Evidence of transmission will be defined as a respiratory illness developing within a week of another family member (viral shedding occurs mostly in the 5 days after symptoms commence and the average incubation period is 2 days). We will assess the implications of using different cut-offs in defining both symptomatic RTIs and the time defining transmission of RTIs.
- **Secondary. Attendance at the GP practice, and use of health service resources: Notes review.** *We hypothesize that the intervention will reduce the number of health service contacts by reducing the number of episodes.* At the end of the study all patients' GP notes will be reviewed to document admission to hospital for respiratory or cardiovascular complications, whether patients attended the GP for their ILI or other respiratory tract infections, whether antibiotics or antivirals were prescribed, and/or any subsequent referrals. Assessment of the notes will be made blind to group, and has been shown to be reliable and unbiased.
- **Attitudes and adherence to infection control behaviours.** *We hypothesize that the intervention will change attitudes, beliefs, intentions, and behaviour.* We will assess attitudes, beliefs, intentions, and self-reported adherence for each behaviour on 7 point Likert scales both in the pilot study (after 1 month and 3 months), and in the main trial at the end of the winter (we will randomly choose 1:20 patients for this outcome). These outcomes will be measured in both groups in the main trial only at the end of the winter, to minimise any effect on behaviour change of administering questionnaires in the control group. These outcomes will allow us to check whether the intervention is successful in effecting change and whether outcomes of the intervention are mediated by changes in these variables. To accompany the winter illness questionnaire we will use an adherence questionnaire (the 'Problematic Experiences of Therapy Scale'; PETS) that we have

used in previous studies, including the MRC ATEAM trial, and two vertigo trials. To reduce social desirability effects on reporting of adherence, the PETS asks patients to what extent they have been prevented from carrying out the intervention by socially acceptable reasons (e.g. symptoms too severe or aggravated by the intervention; doubts about efficacy; uncertainty about how to carry out the intervention; practical problems such as lack of time or opportunity, forgetting). They are only then asked how often and over how many weeks/months they adhered to each aspect of the intervention. To compare the effects of the intervention as a whole with the effects of the website and the target behaviours, in addition to the main intention-to-treat analysis we will carry out per protocol analyses to determine the effectiveness of the intervention in a) those who logged on to the website and b) those who reported adhering to each of the different target behaviours. We will also examine whether the website was equally effective for all sections of the target population (based on age, sex, family factors, deprivation). For the purpose of these analyses, we will supplement and validate the PETS scores using the prospective records from the web-based diary of compliance to the behaviours in each episode of family respiratory illness (completed by the intervention group only).

- **Socio-demographic and comorbidity data.** We will collect age, gender, social indices based on post code (to calculate the index of material deprivation), co-morbidities from the notes where available, and educational level from the patient. This data will document the generalisability of the sample, the similarity of trial groups, and explore effect modification due to deprivation or other demographic variables (although we did not find effect modification previously). The issue of deprivation is relevant since currently 25% of those without web access cite costs of equipment or cost of access as a contributory factor to limiting access. We will document how deprivation (measured by the index of material deprivation based on post code) relates both to uptake and effectiveness of the intervention.
- **Diagnostic substudy.** This study will assess the extent to which ILI report by participants is laboratory confirmed influenza (based on pharyngeal samples transported in viral transport medium). This will allow some explanatory information for the trial results (transmission according to the type of viral illness); assessment of the generalisability of the results; and information to assess diagnostic spectrum bias. There is no widely accepted definition of influenza like illness but most definitions have a combination of fever plus other respiratory or systemic symptoms. Based on RCGP weekly sentinel practice returns we will inform all patients who have agreed to the virological study to commence this substudy when influenza virus is circulating in the community. This is necessary since we already know that the predictive values will be poor when influenza is not circulating. Patients with fever of >37.5, plus a respiratory symptom (sore throat, cough, coryza) plus a systemic symptom (chills, prostration, headache, severe fatigue, severe muscle aches, severe malaise) will record the range of symptoms and temperature twice daily (using tempadot thermometers) for at least 5 days; the symptoms recorded will be based on previous clinical studies in influenza and respiratory infections. We have used similar diaries successfully. Patients will be instructed to take their own viral samples using the simplest method possible: our provisional proposal is to do this by gargling with tap water into a universal container ([name] lab have recently shown this method to provide valid PCR results compared to conventional naso-pharyngeal swabs and transport media (unpublished data)). The validity of this can be confirmed during the pilot phase, and nasopharyngeal swabs will be used as necessary; the feasibility phase will also explore how much written and/or telephone support is needed for patients to take and send their own samples. Virological samples will be posted first class to [name] laboratory (Glasgow) to facilitate standard analysis using PCR to assess the presence of influenza and other respiratory viruses (Influenza A, B, C; Paraflu 1, 2, 3, 4; Coronaviruses; RSV; HMPV (human metapneumovirus); Adenovirus; Bocavirus). Patients will be asked both for the last episode of ILI and the last respiratory infection whether they contacted the doctor (or NHS Direct); and will be asked at the end of the diary whether for this episode they have contacted the doctor (or NHS Direct). The patients participating in this study will also be asked whether they would be prepared to provide similar samples and clinical information should a pandemic occur: having a network of patients in the community already experienced and able to provide clinical forms and samples at short notice could be invaluable in providing information about the clinical presentations during a pandemic; a series of practices with many patients in each area will complement the information generated from the MRC flu watch study (which is collecting information from fewer patients in each practice and over a much wider area).

**3.11. Will HSR issues be addressed.** We think it likely that the intervention will be both effective, and since it is very inexpensive therefore cost-effective. However, this cannot be assumed – for example it is not impossible that a website might increase anxieties about influenza and increase contact rates. Therefore the resource use incurred and potentially saved (particularly any change in the nature of health service contacts with primary care services) needs to be quantified carefully. We will collect cost and outcome data, to allow an economic evaluation, both disease specific (£/episode and per symptom free day) and generic (£/QALY). The former will be based on the primary outcomes, the latter on QALY values. EuroQol (EQ-5D) - the 5 item EuroQol - will be

filled in at baseline and during an ILI or respiratory infection (at different days to provide an estimate of the profile of EQ-5D for an ILI) for those patients doing the more intensive diagnostic sub-study, to provide a measure of quality of life. Patients who are admitted to hospital will be asked to return a post card informing the study team that they have been admitted and will then be sent another 5 item Euroqol to complete after discharge. EQ5D results will be compared with the other outcomes measured in the study and more disease specific measures of cost effectiveness will be estimated if and as appropriate. Modelling pre-trial in the first three months will be carried out to help inform power calculations for economic outcomes, help the design of data collection, and set up and prepare for the modeling that would be necessary post trial. Regarding the main analysis at the end of the study we will estimate the intervention and follow-up related costs, including the time taken to train staff, surgery attendance, admissions and referrals. Resource use data will be collected by notes review, GP and nurse documentation (e.g. of consultation time) and patient self-report. The use of the Hants/IOW Clinical Data Repository, which included all GP and hospital data, will be piloted to check if it can provide the requisite data electronically. If so, this would be validated against a sample of GP and hospital case notes. We will also explore streamlined computerised methods of collecting data on resource use from GP notes since most practices are likely to be computerised. Although our primary analysis will be from the health service perspective we are also interested in the personal costs. Thus during piloting and in qualitative work we will explore the range of resource use - e.g. over the counter medication, transport to GP surgery – to make sure we are not missing important costs. In the final analysis of the trial, resources will be valued using national rather than local unit costs wherever possible to aid generalisability of the results. The economic analysis will assess the cost per episode and per symptom day prevented and cost per quality adjusted life year (QALY) from a health service perspective. Sensitivity analysis will explore varying the parameter values of greatest uncertainty. The model will be informed by a detailed review to be done in the feasibility phase of the project of the models prepared for the 3 reviews of influenza antivirals prepared for NICE (<http://www.nice.org.uk/>).

**3.12 What is the proposed sample size?: Transmission of ILI.** All calculations are based on the patient randomised (the index person). We assume that our more rigorously developed, interactive, and tailored intervention will have an NNT of at least 25 and an OR of 0.76 - very slightly better than the previous booklets which had none of these features (OR 0.80, NNT 25). There are other reasons to assume this is a reasonable (if not conservative) effect size: people who have attended with respiratory infections are slightly more likely to be interested in participating, and in this group the effect size from previous study was significantly larger; a 20% reduction in transmission is the effect size seen in most of the studies of handwashing alone; a larger effect on behaviour is also likely given the heightened public concern about ILI since the above studies. If 10% suffer ILI (<http://www.eurosurveillance.org/em/v10n12/1012-223.asp>; <http://www.niaid.nih.gov/factsheets/flu.htm>), the average household size is 2.4 individuals (<http://www.statistics.gov.uk>) i.e. 24% can be affected by the transmission of ILI either to or from the index patient, and 20% of those with no intervention will develop ILI, then 15,074 patients are needed (assuming two-sided significance level of 5% and 80% power), or 16,000 to allow some leeway in assumptions (see table below). **Transmission of RTIs.** 16000 will have greater power to detect transmission of all RTIs, and for continuous outcomes this sample size will be extremely powerful (see table). **Nested diagnostic study.** We assume that: at least 10% of the index trial cohort will report ILI, i.e. approximately 1600; 50% will agree to the virological sub study (n=800) (based on the numbers agreeing to more intensive investigation in a current microbiological study of URTI in our group); flu virus is isolated in at least 50% of individuals presenting with ILI when ILI is circulating; and that 30-50% of patients are likely to contact the doctor then in the cohort reporting ILI then we should be able to estimate the positive predictive value of a clinical diagnosis in predicting laboratory confirmed influenza with 95% confidence intervals of +/- 10% in both the sample attending the doctor (n=240-400) and the sample not attending (n=400-560). For the analysis of the likely positive and negative predictive values (of symptoms, temperature) at each stage in the illness (12hours,24hours,36 hours etc) we will have greater precision since we can use the whole sample who agree to the diagnostic study.

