#### **Main trial:**

Adult patients (aged 18+) living with at least one other person. Patients whose GP notes show a skin problem that may affect handwashing ability, and those who live in households where no one else is willing to provide illness feedback will be excluded. Participants will be randomised to:

- 1) Access to an interactive website by a personal password, providing tailored advice; this will be reinforced by email prompts and reminders to use the website; patients will be advised to use hand-washing and a range of infection control measures both within and outside the family
- 2) Normal care (access to the website at the end of the trial)

**Outcomes:** transmission of ILI and other infections between family members, severity and duration of ILI and other respiratory infections.

**Virological sub study:** based on laboratory confirmed virological diagnosis, we will document the nature of circulating viruses, estimate whether transmission differs according to the type of viral illness; provide estimates of the predictive value of clinical symptoms and signs according to the spectrum of illness (defined by contact with the NHS and prior duration of illness).

**3.2 What is the proposed trial design.** An RCT, with a development phase and a nested viral study.

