
#### Range of effect sizes likely for the trial (bold= our target for that outcome)

| Effect size                                                                                                               | N per group
(with complete outcomes where
transmission of infection possible
either to or from the index person) | Total N required for ILI
(assuming 24% where transmission
possible to or from index person; and
allowing for 20% loss to follow-up) | Total N for all respiratory
infections (assuming all cohort where
transmission possible; and allowing
20% loss to follow-up) |
|---------------------------------------------------------------------------------------------------------------------------|---------------------------------------------------------------------------------------------------------------------------|----------------------------------------------------------------------------------------------------------------------------------------------|---------------------------------------------------------------------------------------------------------------------------------------|
| Dichotomous outcomes e.g. transmission
(alpha=0.05 beta=0.2)                                                   |                                                                                                                           |                                                                                                                                              |                                                                                                                                       |
| 20% vs 18% (NNT 50; OR 0.88)                                                                                       | 6039                                                                                                                      | 62,906                                                                                                                                       | 15,098                                                                                                                         |

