| 20% vs 17% (NNT 33; OR 0.82)                                                                                              | 2629                                                                                                                      | 27,386                                                                                                                                       | 6574                                                                                                                                  |
| 20% vs 16% (NNT 25 OR 0.76)                                                                                        | 1447                                                                                                                      | 15,074                                                                                                                                | 3618                                                                                                                                  |
| 20% vs 15% (NNT 20 OR 0.71)                                                                                               | 906                                                                                                                       | 9,438                                                                                                                                        | 2266                                                                                                                                  |
| Continuous outcomes e.g. days illness
(alpha=0.01 (multiple outcomes); beta=0.1)
standardised effect sizes |                                                                                                                           |                                                                                                                                              |                                                                                                                                       |

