**Main trial analysis.** The data will be analysed according to the Statistical Analysis Plan which will be approved by the Trial Steering Committee before the commencement of any analysis. One intention to treat analysis will be performed. We will assess the transmission of ILI or other respiratory tract infection - i.e. either between the index case and family members or from family members to the index person - using multiple logistic regression, the duration of symptoms labelled moderately bad days using multiple linear regression, and attendance at the GP surgery using Poisson regression, controlling for stratifiers. We found in our previous trial of leaflets there were no significant clustering effects by practice; our analysis will be based on the index patient to avoid a design effect due to family clustering. For the symptom data the main analysis will be of symptoms in the index person but a secondary analysis will assess symptoms reported for all other family members averaged at the level of the family. Confidence intervals will be reported, and the study will be reported in accordance with the CONSORT statement.

**Subgroup analysis (using two sided 1% significance levels).** We will assess whether any of the stratification variables are effect modifiers; whether age, deprivation, education level, and co-morbidities predict outcomes or are effect modifiers; whether self reported adherence to each behaviour determines outcome.

**Diagnostic study analysis.** We will assess the sensitivity specificity likelihood ratios and positive and negative predictive values for symptoms and temperature in the whole sample, and in the sub-samples who would not contact their practice or NHS Direct (either in this or in past episodes). We will use logistic regression to determine which symptoms (and or temperature) individually or in combination are most predictive. We will also estimate the predictive value of symptoms (and or temperature) for laboratory diagnosed influenza at 12 hours after the start of the illness, then at 24 hours, 36 hours, 48 hours, and 48+ hours.

**3.20 Has a pilot study been carried out?** We have not piloted this precise protocol, but have recruited very similar trial cohorts using similar recruitment mechanisms, and have developed similar websites

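### Several ILI and RTI outcomes share the primary label with no ranking; alpha is reduced only for continuous outcomes, and the first-named outcome is not sized

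*Protocol*

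**What the plan says.** - **Section 3.9/3.10 (outcome measures).** The primary outcome is "Episodes of ILI and RTI, their duration and transmission in families". The stated hypothesis is: "We hypothesize that the intervention will reduce the number of episodes (by reducing transmission) and hence the number of days with symptoms". No outcome is singled out and no testing order is given.
- **Section 3.12 (sample size).** The calculation opens with ILI transmission, "assuming two-sided significance level of 5% and 80% power", and gives 15,074, raised to 16,000.
- **Table of effect sizes in section 3.12.** Dichotomous outcomes are sized at "alpha=0.05 beta=0.2". The bold ILI target is the row "20% vs 16% (NNT 25 OR 0.76", with 15,074 in total. RTI transmission has a separate bold target, 15,098, for 20% vs 18% at the same level. Continuous outcomes are sized at "alpha=0.01 (multiple outcomes); beta=0.1", with a bold RTI target of 3,314. No row covers the number of episodes.
- **Section 3.17-.18 (main trial analysis).** Transmission is analysed by logistic regression, "the duration of symptoms labelled moderately bad days using multiple linear regression", and GP attendance, which is a secondary outcome, by Poisson regression. Analysis follows a SAP that is not at hand.

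**The concern.** The outcome section, the sample size and the significance levels do not point to the same primary outcome. The hypothesis is about episodes, and through them symptom days, with transmission as the mechanism. The sample size rests on the mechanism. The levels differ by type of outcome: a multiplicity allowance is made for continuous outcomes, while two transmission outcomes each keep the full 5%.

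If the designation stays open, a favourable result on any outcome under the primary label could be presented as the trial's main finding. The error rate attached to that conclusion would then exceed the 5% behind the sample size. This matters more here because section 3.5 says patients cannot be blinded, illness is self-reported, and section 3.9/3.10 plans to vary the cut-offs that define RTI and transmission.

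**Working it through.** **1. Reproduce the plan's sample sizes.** Inputs are from section 3.12 and its table: two-sided alpha 0.05, power 80%, 24% of the cohort at risk of ILI transmission, 20% loss. The formula is the usual one for two proportions with pooled variance and no continuity correction:

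n = [1.96·√(2p̄(1−p̄)) + 0.8416·√(p₁(1−p₁)+p₂(1−p₂))]² / (p₁−p₂)²

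- ILI, 20% vs 16%: n = 1447 per group, as stated. 1447/(0.24 × 0.80) = 7536.5, rounded up to 7537 per group, 15,074 in total. Reproduced.
- RTI, 20% vs 18%: n = 6039 per group, as stated. 6039/0.80 = 7548.75, rounded up to 7549 per group, 15,098 in total. Reproduced.
- Continuous, standardised effect 0.15, alpha 0.01, power 90%: n = 1323 per group, against 1325 stated. This is close enough.

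The arithmetic of the table is sound. The question is which outcome it serves.

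**2. Chance of at least one false-positive primary result.** If the tests were independent, this is 1 − ∏(1 − αᵢ).

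- Two transmission tests (ILI, RTI) at 0.05: 1 − 0.95² = 9.75%.
- Adding two duration tests at 0.01: 1 − 0.95² × 0.99² = 11.5%.
- Adding two episode tests at 0.05 (assumed, since no level is stated): 1 − 0.95⁴ × 0.99² = 20.2%.

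The outcomes are positively related, so independence gives the upper end. With test statistics equally correlated at ρ (also an assumption):

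| Tests | independent | ρ = 0.5 | ρ = 0.7 |
|---|---|---|---|
| 2 transmission at 0.05, 2 duration at 0.01 | 11.5% | about 10% | about 9% |
| the same plus 2 episode tests at 0.05 | 20% | 16% | 13% |

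**3. What designating ILI transmission does to power.** Power = Φ{[|p₁−p₂|√n − 1.96·√(2p̄(1−p̄))] / √(p₁(1−p₁)+p₂(1−p₂))}.

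- Protocol's basis, at-risk patients only: n = 16,000 × 0.24 × 0.80 / 2 = 1536 per group, 20% vs 16%. The numerator is 0.04 × √1536 − 1.96 × 0.5433 = 0.503 and the denominator 0.5426, so the ratio is 0.927 and power is 82%.
- All randomised patients, assuming no events outside the 24%: the rates become 0.24 × 20% = 4.8% and 0.24 × 16% = 3.84%, with n = 16,000 × 0.80 / 2 = 6400 per group. The numerator is 0.0096 × 80 − 1.96 × 0.2875 = 0.204 and the denominator 0.2874, so the ratio is 0.711 and power is 76%. Reaching 80% needs 7040 per group with outcomes, or 2 × 7040/0.80 = 17,600 in total.

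**4. The alternative of two co-primaries.** With ILI and RTI transmission each at 0.025, ILI needs 1753 per group, 2 × 1753/(0.24 × 0.80) = about 18,260 in total. Power at 16,000 falls to about 74% for each.

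**The case against.** The other side has real points.

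- **Multiplicity is not ignored.** The 1% level for continuous outcomes is an explicit allowance. A reader might infer that the plan has no error control, or take six tests at 5% and quote 1 − 0.95⁶ = 26%. The stated levels do not support either. The allowance is partial, however: it appears only in the sample-size table and leaves both transmission tests at 5%.
- **There is an implicit lead outcome.** Section 3.12 starts from ILI transmission and takes the total from it, and RTI follows as something that total can also detect. A reader might infer that the trial has no usable test of success. That goes too far: a lead outcome can be recognised, but it is not designated where outcomes are defined.
- **The number of tests is a reading.** The analysis section could mean one combined transmission test or one for each illness. The protocol states no rule that any one positive result counts as success.
- **Some detail belongs in the SAP.** The model for episode counts and the level of the main tests may be there, so their absence from section 3.17-.18 is not itself a fault. What remains is a mismatch inside the protocol: episodes head the primary list, while the sizing rests on transmission and days.
- **Section 3.1 is not a rival primary list.** Its line, "transmission of ILI and other infections between family members, severity and duration of ILI and other respiratory infections", is a short synopsis of outcomes, not labelled primary.

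None of this removes the central point. Which outcome is primary is for the protocol to fix, and a SAP that chose one would leave section 3.9/3.10 uncorrected.

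**Conclusion.** The point holds in this form: the primary label covers episodes, duration and transmission for both ILI and RTI, with no single primary and no hierarchy. The sample size serves ILI transmission, RTI transmission has a second target at a full 5%, the reduction to 1% applies only to continuous outcomes, and the number of episodes is not sized.

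On the stated levels the chance of at least one false-positive primary result is about 9 to 12%. It is about 13 to 20% if two episode tests at an assumed 5% are included. These figures assume separate ILI and RTI tests, no true effect on any outcome, success claimed on any one of them, and a common correlation between 0 and 0.7. They show the size of the problem and do not describe a rule the protocol states.

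**What to change.** Before any analysis, amend section 3.9/3.10 to designate one primary outcome. ILI transmission to or from the index person, at two-sided 5%, is the one the sample size supports. Make RTI transmission, number of episodes and moderately bad symptom days secondary. Give them a testing order, or a level for each outcome, and use the same one in sections 3.12 and 3.17-.18.

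State the analysis denominator for the primary outcome and make the power statement match it. On the at-risk basis 16,000 gives about 82%. With all randomised patients as denominator it gives about 76% under the no-other-events assumption, and 80% would need about 17,600.

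Cost: mostly protocol wording. The sponsor gives up claiming primary success on several outcomes, and the stated power may become slightly less favourable. If the sponsor prefers ILI and RTI transmission as co-primaries, splitting alpha equally costs power (about 74% each at 16,000) or requires about 18,300 patients.
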